### Primary outcome measures

All participants will be followed for 12 months following baseline assessment to record the number of falls. Falls, defined as "an unexpected event in which the participant comes to rest on the ground, floor, or lower level" [43] will be monitored using monthly mail-out calendars. When a fall occurs, specific details about fall injuries will be obtained through structured telephone interviews. If falls calendars are not returned at the end of each month, research staff will contact the participants by telephone to obtain the missing data. Consistent with the recommendations of the Prevention of Falls Network Europe group, three falls outcomes will be used as the primary outcomes: the number of fallers, the number of multiple fallers and the falls rate. As a safety measure, the time to first fall will be recorded as a secondary measure to reflect adverse events from the intervention [43].

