### Sample size

The sample size for the study has been determined *a priori *using an appropriate sample size formula [67]. A sample size of 143 participants in each group provides 80% power to detect a 30% reduction in the intervention group in the primary outcome of the percentage of fallers. This reduction in falls was based on the following: (i) a falling rate of 60% in the control group (as has been observed in older people with foot pain in a previous risk factor study by Menz et al [12]), and (ii) a falling rate of 42% in the intervention group (which equates to a 30% reduction in the number of fallers, recently demonstrated in a similar multifaceted study by Clemson et al [68]). We chose an alpha level of 0.05 and allowed for a drop-out rate of 15%. To allow for unforeseen circumstances we will aim to recruit 300 participants (i.e. 150 per group).

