### Statistical analysis

Statistical analysis will be undertaken using SPSS version 14.0 (SPSS Corp, Chicago, Ill, USA) and STATA 8 (Stata Corp, College Station, Tex., USA) statistical software. All analyses will be conducted on an intention-to-treat principle using all randomised participants [69]. Missing data will be replaced with the last score carried forward. Demographic characteristics and baseline data will be summarised by descriptive statistics. Consistent with the recommendations of the Prevention of Falls Network Europe group [43], three falls outcomes will be used as the primary outcomes: the number of fallers, the number of multiple fallers and the falls rate. The number of fallers and multiple fallers (two or more falls) will be compared by calculating relative risks. The number of falls and falls rate per person per year in the two groups will then be compared using negative binomial regression models. This approach takes into account all falls and adjusts for varying duration of follow-up [70,71]. The continuously-scored secondary outcome measures at baseline and the six month follow-up appointments will be compared using analysis of covariance with baseline scores and intervention group entered as independent variables [72,73].

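### Fallers (the powered outcome) and multiple fallers are compared by relative risks with no allowance for follow-up time; combined with carry-forward over all randomised participants, unequal withdrawal biases them

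*Protocol article*

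**What the plan says.** The Statistical analysis section of the protocol article fixes the method for each of the three primary falls outcomes.

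- Fallers and multiple fallers: "The number of fallers and multiple fallers (two or more falls) will be compared by calculating relative risks". No term for time at risk is given.
- Falls rate: "The number of falls and falls rate per person per year in the two groups will then be compared using negative binomial regression models". The next sentence adds: "This approach takes into account all falls and adjusts for varying duration of follow-up". In context this refers to the negative binomial models.
- Analysis set: "All analyses will be conducted on an intention-to-treat principle using all randomised participants".
- Missing data: "Missing data will be replaced with the last score carried forward".

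The Sample size section powers the trial on the percentage of fallers (60% v 42%): "A sample size of 143 participants in each group provides 80% power to detect a 30% reduction in the intervention group". On loss it says "We chose an alpha level of 0.05 and allowed for a drop-out rate of 15" (per cent).

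Under Primary outcome measures, falls are recorded on monthly calendars over 12 months. Staff telephone anyone whose calendar does not come back. On timing, "the time to first fall will be recorded as a secondary measure to reflect adverse events from the intervention".

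**The concern.** The plan expects follow-up to vary, and corrects for it in one of three primary outcomes. The two left uncorrected include the one that sets the sample size.

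Faller status can only accumulate with time at risk. Taken together, the rules above treat a person who leaves fall-free after one month exactly like a person observed fall-free for a year. A person who leaves after one fall is fixed as not a multiple faller. The arm that loses more people, or loses them earlier, then shows fewer fallers for a mechanical reason. If that is the intervention arm, the bias imitates benefit. If it is the control arm, the bias hides benefit. The faller outcomes could also disagree with the follow-up-adjusted falls rate without any clinical reason.

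**Working it through.** **The plan's own figure.** Inputs from the Sample size section: 60% v 42%, alpha 0.05 (taken as two-sided), 80% power, 15% drop-out. The two-proportion formula without continuity correction gives

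n = [1.96 × √(2 × 0.51 × 0.49) + 0.842 × √(0.6 × 0.4 + 0.42 × 0.58)]² / 0.18² = 119.9, so 120 per arm.

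120 / 0.85 = 141.2, so 142, against the stated 143. The sample size reproduces.

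**Assumptions for the check.** Fall hazard is constant within arm: h = −ln(0.40) = 0.916 per year for 60% fallers, and −ln(0.58) = 0.545 for 42%. There are 150 per arm. A fraction d of an arm leaves, with exit times uniform on [0, T] and unrelated to falls. Leavers with no recorded fall count as non-fallers, as the stated rules imply. The article gives only the overall 15%, so the arm splits and exit timing are assumptions.

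**Formulas.** P(fall before exit) = q = 1 − (1 − e^(−hT)) / (hT). Observed faller proportion = (1 − d) × p + d × q.

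For p = 0.60, q is 0.345, 0.198 and 0.106 when exits are spread over the first 12, 6 and 3 months. For p = 0.42, q is 0.229, 0.125 and 0.065.

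**Equal loss, 15% in each arm, true 60% v 42%**

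| Exits over | Control | Intervention | RR | Power |
|---|---|---|---|---|
| 12 months | 0.562 | 0.391 | 0.70 | 84% |
| 6 months | 0.540 | 0.376 | 0.70 | 82% |
| 3 months | 0.526 | 0.367 | 0.70 | about 80% |

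The ratio holds, but both 12-month risks are understated.

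**No true effect (60% in both arms), loss of 19% intervention v 11% control**

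| Exits over | Control | Intervention | RR | Chance of a false benefit (nominal 2.5%) |
|---|---|---|---|---|
| 12 months | 0.572 | 0.552 | 0.96 | 5.4% |
| 6 months | 0.556 | 0.524 | 0.94 | 8.1% |
| 3 months | 0.546 | 0.506 | 0.93 | 10.1% |

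Example for the first row: control 0.89 × 0.60 + 0.11 × 0.345 = 0.572; intervention 0.81 × 0.60 + 0.19 × 0.345 = 0.552. The difference is 0.020 and its standard error 0.057, so the chance of exceeding 1.96 standard errors in favour of the intervention is 5.4%.

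**True 60% v 42%, loss of 10% intervention v 20% control**

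| Exits over | Control | Intervention | RR | Power |
|---|---|---|---|---|
| 12 months | 0.549 | 0.401 | 0.73 | 73% |
| 6 months | 0.520 | 0.390 | 0.75 | 61% |
| 3 months | 0.501 | 0.385 | 0.77 | 53% |

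**Multiple fallers.** Take Poisson falls, no true effect, loss of 20% intervention v 10% control, and exits over the year. P(two or more falls in 12 months) = 1 − 0.40 × 1.916 = 0.2335, and for leavers it is 0.090. The observed proportions are 0.8 × 0.2335 + 0.2 × 0.090 = 0.205 and 0.9 × 0.2335 + 0.1 × 0.090 = 0.219. The RR is 0.935, against 0.956 for fallers under the same loss.

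**A comparison that uses follow-up time.** 60% v 42% is a hazard ratio of 0.545 / 0.916 = 0.594, which needs 117 first falls (Schoenfeld). With 143 per arm and 15% loss spread over the year, about 143 × (0.562 + 0.391) = 136 are expected, giving about 86% power. In 4,000-run simulations with no true effect and control v intervention loss of 10% v 20%, 5% v 25% and 0% v 30%, two-sided type I error was 7.7%, 16.0% and 27.8% for the crude test and 4.6% to 5.5% for the log-rank test.

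**The case against.** **The bias is not independent of the missing-data rule.** Every figure above needs leavers to be scored as non-fallers. If their status were left missing and the proportion taken among people followed for 12 months, everyone counted would have equal time at risk. With exit unrelated to falls, both arms would then show 60% and the RR would be 1.00. This stands. A reader might infer that the relative risk is faulty whatever is done about carry-forward, but the article does not support that. The problem lies in combining an unadjusted relative risk, all randomised participants and carry-forward.

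**The article does not show unequal loss.** Its Discussion cites exercise adherence of 78%, or 63% when people who dropped out of the exercise are included. The 19% used above is 1 − 63/78, which is an adherence ratio and not attrition from falls follow-up. Someone who stops exercising can still return calendars. It is tempting to read these figures as evidence that the intervention arm will lose more people, but they serve only to illustrate a split.

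**There are safeguards.** Telephone retrieval fills in missing months, the falls rate is adjusted for follow-up, and time to first fall is recorded. These help, and a discrepancy between outcomes would be visible. However, retrieval cannot supply follow-up after withdrawal, and time to first fall is listed as a safety measure rather than as the analysis of fallers.

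**An unseen analysis plan might refine the estimate.** That is possible, and the lack of adjustment is inferred from the wording. But the article itself states the effect measure, the analysis set and the carry-forward rule, and attaches the follow-up adjustment to the rate models alone.

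**Conclusion.** The concern holds in a limited form. Under the stated rules, the powered outcome and the multiple-faller outcome ignore time at risk, while the falls rate does not.

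The direction and size of the bias depend on differences between arms in how many leave and when. Equal loss does little harm to the ratio and mainly understates the absolute risks. An 8-point imbalance spread over the year moves a null RR to 0.96; withdrawals concentrated in the first three months take it to 0.93. A 10-point imbalance the other way can cost a good part of the power.

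A reader might infer that withdrawal alone could produce the planned 30% reduction. That would need an extreme pattern, such as 30% of the intervention arm and none of the control arm leaving at the very start (0.70 × 60% = 42%), and nothing in the article suggests it. The results rest on constant hazards, exit unrelated to falls, and assumed splits and timing. The sample size itself is sound. The point is worth correcting because the remedy is cheap.

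**What to change.** For the two faller outcomes, state that a no-fall status is not carried forward. Censor each participant at the last completed calendar or telephone contact. In each arm, estimate the 12-month risk of a first fall (fallers) and of a second fall (multiple fallers) by Kaplan-Meier. Report the ratio of the two risks with a bootstrap or delta-method confidence interval. A complementary log-log model with log follow-up time as offset is an alternative. Keep the crude proportions as description.

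This keeps the relative-risk scale and every randomised participant, and puts all three primary outcomes on a follow-up-adjusted basis.

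The cost is a few sentences and minor programming. Calendars are already monthly and time to first fall is already recorded, so no visits or data are added, and the power check above gives no reason to enlarge the sample. The downside is the assumption that censoring is unrelated to falls within arm. It would fail if falls or frailty led people to withdraw, but the planned negative binomial model makes a similar assumption.

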## Discussion

This study is a randomised trial designed to investigate whether a multifaceted podiatry intervention can prevent falls, enhance balance and reduce disabling foot pain in older people. It will report on all the outcome measures recommended by Prevention of Falls Network Europe, a collaborative project to promote best practice in research in falls in older people. These outcome measures are falls, fall injury, physical activity, psychological consequences, and generic health related quality of life [43].

While current guidelines [20,32] generally recommend multifactorial interventions, a recent meta-analysis has highlighted that a single targeted intervention can be as effective as multifactorial fall prevention programs [74]. The current study targets podiatry interventions using a multifaceted approach. The trial interventions are all management strategies commonly used by podiatrists for treatment of foot-related problems in the general population. While there is some evidence that these interventions can improve balance, this is the first trial to combine specific foot and shoe-related interventions in a falls prevention trial.

A key factor in determining the efficacy of a falls prevention intervention is the degree of adherence to the program. While we do not expect any difficulties to arise in relation to the "usual care" component of the study, adherence may be more difficult to achieve in relation to the provision of new footwear and the home-based exercise program. Indeed, previous studies have indicated that compliance with use of therapeutic footwear has been shown to be low in people with diabetes [75] and rheumatoid arthritis [76] and a recent survey of emergency department physicians indicated that compliance with footwear recommendations to prevent falls was poor, due to "stubbornness and vanity" [77]. However, a recent evaluation of people attending falls clinics reported that 85% had partly or fully complied with footwear advice, suggesting that older people who are aware of their risk of future falls may be more likely to adhere to footwear recommendations [78].

In a review of 21 randomised trials of exercise including middle and older aged adults, the average rate of adherence to exercise training (typically measured by frequency of exercise) was reported to be 78%, reducing to 63% when data from participants who dropped out of the exercise intervention was included [79]. However, there is evidence that strength training can be successful when undertaken at home alone [80] and that many older people prefer to exercise at home [81]. The use of exercise sheets with written descriptions and diagrams [82], training diaries [83] and continued support through either mail or telephone contact from the exercise instructor [84] have all been shown to increase adherence. To optimise adherence in our trial, we intend to utilise each of these strategies.

In summary, this project is the first randomised trial to be conducted to evaluate the efficacy of podiatry in improving balance and preventing falls in older people. The intervention has been pragmatically designed to ensure that the study findings can be implemented into clinical practice if found to be an effective falls prevention strategy. Recruitment for the study will commence in July 2008, and we expect final results to be available in mid 2011.
